#### Participant Retention and Remuneration

Participants received compensation of a US $20 local grocery store gift card for each data collection event (T0, T1, T2, and T3). Additional rewards were built into the intervention to encourage participation and retention. Cohort 2 participants served as the active control group when not receiving the intervention. The active control consisted of monthly presentations on wellness topics not related to nutrition and bingo games led by our research team, in which they could win a US $5 local grocery store gift card. Furthermore, voluntary peer navigators, who were participants enrolled in the study and attending the center, were recruited from most sites to assist any participant requiring extra help with Zoom (Zoom Video Communications, Inc) session login, survey completion, or troubleshooting challenges within their capacity.

### Intervention Design

The City of San Antonio Senior Services Division, which oversees the CMP in Bexar County, along with Older Adults Technology Services (OATS) and the University of Texas at San Antonio (UTSA), researchers with expertise in nutrition and physical activity devised the Digital Nutrition Education Intervention. The intervention included a 5-week technology intervention, designed to address defining features of the digital divide such as access, knowledge, and usage. The 15-week online nutrition course aimed to improve food security and increase overall diet quality, while providing accurate information about nutrition and physical activity through virtual sessions.

### Formative Work

A pilot study (5 weeks) was conducted in June and July 2022 with 4 older adults who attended a local community center located in San Antonio and completed a technology class with OATS in May 2022. The community center does not have a congregate meal program. All baseline and posttesting measures and created the surveys for feedback were tested in the pilot study. Pilot data were used to inform the full 15-week intervention. All participants were satisfied with the nutrition topics, recipes, and resources provided, as well as the Friday lunch Zoom socials. A total of 75% were satisfied with the goal sheets and weekly surveys in Google Forms. All participants were satisfied with Google Classroom, but some preferred accessing the class materials by email. During the pilot study, only a single session was offered to participants. Based on their feedback, participants recommended that multiple sessions be provided to enhance scheduling, flexibility, and accommodate different availability. Process evaluation materials were finalized for the technology and nutrition intervention to document fidelity, knowledge gained, and participant satisfaction.

The creation of both the technology and nutrition intervention was informed by an advisory board consisting of UTSA researchers, key Department of Human Services (DHS) and OATS staff, and focus groups consisting of older adult CMP participants. Researchers conducted 14 focus groups with 109 CMP participants in Spring 2022 to determine the choice of technology device and nutrition topics to be incorporated into the nutrition intervention plan. Participants preferred iPads (Apple Inc) over LG tablets due to their big screen, brightness, and user-friendliness. The focus group informed the nutrition topics covered: food security and support resources, fruits and vegetables, whole grains, protein, lean meats, low-fat dairy, healthy snacks, hydration, sodium, healthy eating on a budget, reading food labels, dietary supplements, and food safety. Chronic disease-specific topics were not covered and were linked to the prevention and management of nutrition-related chronic conditions. Special emphasis on food security and the Supplemental Food Assistance Program, and other assistance programs that may help alleviate the cost of food. Three out of 5 older adults are eligible for assistance programs and do not apply for benefits [39]. Additional assistance was provided if food access was an issue. Many grocery stores and food delivery services require digital apps or online ordering, which was covered during the intervention.

### Technology Intervention

OATS is a nonprofit organization established in 2004 with a mission to help older adults live better in the digital age. OATS focuses on key areas of financial security, health and wellness, civic engagement and advocacy, social engagement, creative expression, and lifelong learning. Based in New York, OATS expanded to 6 states, including Texas in 2018, with over 26 locations. OATS has served over 30,000 older adults and has engaged San Antonio’s Mayor in the Aging Connected pledge to have 1 million seniors engage online. After participation in technology services, OATS reported 76% of participants felt more connected, 39% reported better health, 44% lost weight, 86% felt less lonely, and 94% felt more connected to the world around them. OATS has over 70 online courses and 45 online videos to support its programming.

The technology intervention addresses three key elements of the digital divide: (1) access to the internet and digital devices; (2) digital literacy or skills; and (3) internet usage and value. Access and use of the internet were reported by 67% of adults 65 years or older in the United States [19]. Although internet usage in older adults has increased significantly over the past 5 years [40], digital inequalities and disparities exist for at-risk populations. Digital inequalities can further describe the digital divide in terms of usage, skills, social support, and self-perception. Older adults who use the internet could have limitations in skill, social support, and attitudes that can further describe passive participation in our digital society [41]. Disparities in racial or ethnic minorities further expand the digital divide and are compounded by low socioeconomic status [42,43].

Using OATS’ expertise in providing technology education and services, enrolled participants received a technology bundle. The technology bundle included a tablet computer device selected by the focus groups and covers 1 year of internet connectivity and technical support provided by OATS. The participants attended a 5-week iPad course that provides information on iPad essentials, introduction to digital culture, and physical activity resources in small groups of less than 15 in person at the CMP sites. In addition, peer navigators (participants who identified as being comfortable in technology skills) were recruited from CMP sites to assist those struggling with technology and having trouble completing weekly tasks in Google Classroom.

### Nutrition Intervention

The nutrition intervention aims to restore and enhance nutrition programming for congregate meal participants online after bridging digital connectivity, access to devices, and the applied use of technology. Key intervention strategies to address technology and nutrition will be used to improve diet quality, food security, physical activity, technology use, and socialization (Figure 2). Long-term maintenance of the online curriculum will be managed by DHS Senior Services program, and the sustainability of the project will be measured after 6 months.

**Figure 2. F2:**
[figure not shown]
Conceptual framework outlining the digital nutrition study design and key components.

Suggestions from the literature recommend soliciting older adult participation in the technical intervention design and considering barriers to technological intervention [31]. Our nutrition intervention was developed in coordination with input from a subset of older adult CMP participants and the registered dietitian from DHS Senior Services. In addition, we designed the intervention based on successful dietary behavioral change interventions and successful digital interventions with older adults by the following: defined and clear topics relevant to older adult health and the population, using proven behavioral theories, using incentives, and sufficient contact. The intervention was informed by the Social Cognitive Theory that addresses intrapersonal and interpersonal influences on behavior change. Weekly goal setting and goal evaluation were incorporated to increase participants’ self-efficacy in eating healthy. Social support systems embedded in the intervention encouraged and rewarded behavior changes. All materials were created at a sixth-grade reading level or below and made available in English and Spanish. Only 1‐2 learning objectives for each topic were created. A digital reward-based program was created to provide incentives for participation and behavior change. Rewards were in the form of digital “badges” like what is used in online sites and applications for achievements [44,45]. The benefits of this system include a no-cost reward system that may motivate participation and signify progress in learning [45,46]. Weekly and monthly rewards were given for attendance and completing weekly tasks which were captured in a digital format. Graduates of the program were given a certificate at a graduation ceremony conducted at the centers in person.

Weekly modules in Google Classroom included nutrition, Microsoft PowerPoint presentations and supplementary resources, handouts, videos, and recipes to enhance learning and practical application. Physical activity resources such as prerecorded (<10 min) classes and resources, videos, and handouts were included to complement the nutrition intervention. The physical activity classes were designed to cater to the specific needs and abilities of older adults, including low-impact activities designed to be gentle on the joints and help improve cardiovascular health, strength, balance, and flexibility. The physical activity classes also provided information on the importance of nutrition and how it can enhance physical performance and recovery.

All sessions were conducted virtually using the Zoom videoconferencing platform. Email reminders for Zoom sessions and links were sent through Google Classroom and provided in Google Calendar. Each week, 3 sessions were conducted in English at different times of the day, and one session was conducted in Spanish, and participants were encouraged to attend live sessions conducted by a registered dietitian or a supervised dietetic student to provide sufficient contact and flexibility. Each session lasted between 40 minutes and an hour and included a Microsoft PowerPoint presentation based on the predetermined weekly topics (Table 1). Time was allocated at the end of each interactive session for questions and answers. One English session and 1 Spanish session were recorded and sent to all participants midway through the week for viewing if they missed attending the live session or if they would like to rewatch.

**Table 1. T1:** Specific topics, learning objectives, clear messaging, and rewards.

Week	Topic	Learning objectives	Clear messaging	Rewards^a^
1	Introduction	Use the tablet to access live and recorded sessions. List possible rewards. Identify ways to document participation.	Document participation and create goals each week. Participate in 4 out of 5 activities per week to receive rewards.	Digital reward Content Attendance
2	Nutrition and Physical Activity for Healthy Aging	Define healthy aging. List ways nutrition and physical activity can prevent or help manage certain diseases. List the food groups of MyPlate.	Good nutrition and regular physical activity can positively impact overall health. MyPlate meals can help you eat healthy foods.	Digital reward Content Attendance
3	Food security and support resources	Define food security. Identify resources that can help with food insecurity. Assess qualifications for any resources to address food security.	Use all the resources you qualify for to help with any food insecurity.	Digital reward Content Attendance
4	Reading food labels	Identify sections of the food label. Identify nutrients that are high or low in a food product.	Reading labels can identify healthy foods.	Digital reward Content Attendance
5	Fruits and vegetables	Describe the health benefits of fruits and vegetables. List the fruit and vegetable recommendations for older adults. Identify fruit and vegetable servings.	Eat a rainbow of fruits and vegetables to gain a variety of nutrients. Eat 2 servings of fruit and 3 servings of vegetables to gain maximum health benefits.	Digital reward Content Attendance
6	Carbohydrates and grains	List foods that contain carbohydrates. Describe the difference between whole and refined grains. Describe how foods with carbohydrates can affect my body.	Many foods contain carbohydrates that are needed to fuel your body. Make half your grains whole.	Digital reward Content Attendance
7	Fats	List foods that contain fats. Describe the health benefits of fats. List fats we need to limit or avoid in our diet.	Healthy fats in our diet can help reduce the risk of certain diseases. Limiting saturated fat and cholesterol is important for a healthy diet.	Digital reward Content Attendance
8	Protein	List foods high in protein. Describe why dietary protein is important for healthy aging. List the recommendations for protein for older adults.	Including adequate protein in our diet can help maintain health. Protein foods come from both plant and animal sources.	Digital reward Content Attendance
9	Season food without salt	Define sodium. Describe how excess sodium relates to health. Describe ways to flavor food without salt.	Flavoring foods without salt can reduce excess sodium intake in the diet.	Digital reward Content Attendance
10	Beverages	Identify healthy beverage options. Describe why hydration is important for older adults.	Consuming beverages helps prevent dehydration. Healthy beverages contain little to no sugar.	Digital reward Content Attendance
11	Healthy snacks	Describe the importance of consuming healthy snacks for older adults. List 3 ways to make healthy snacks.	Healthy snacks can help provide important nutrients in our diet. Healthy snacks contain 2 or more food groups.	Digital reward Content Attendance
12	Eating healthy on a budget	Describe how planning meals helps optimize grocery store visits. List inexpensive easy ways to eat healthy.	Eating healthly on a budget is possible with adequate planning.	Digital reward Content Attendance
13	Dietary supplements	Define dietary supplements. Describe why older adults may need to consume dietary supplements. List ways dietary supplements may cause harm.	Dietary supplements may be recommended in certain situations. Dietary supplements can harm our health if not used appropriately.	Digital reward Content Attendance
14	Food safety	Define foodborne illness. Describe why older adults are more at-risk for foodborne illness. Describe how to prevent foodborne illness.	Older adults are at increased risk for foodborne illnesses. Food may cause illness if not prepared, cooked, or stored properly.	Digital reward Content Attendance
15	Celebration	Celebrate goals achieved and knowledge gained.	Making small changes can improve nutrition choices and healthy habits.	Digital reward Content Attendance Celebration

a Mapping of specific topics to corresponding learning objectives, with emphasis on clear messaging strategies and reinforcement through rewards, developed to support the Digital Nutrition Intervention study.

Participants were required to complete a weekly goal-setting survey, a goal check-in survey, and a week-specific survey. An optional satisfaction survey was sent each week to gather feedback. In addition, optional weekly Zoom social sessions hosted by dietetic and public health students were offered twice a week to facilitate social interaction in the digital space. This was mutually beneficial for the students and the older adults in providing cross-generational interactions to facilitate a greater understanding and empathy for other generations [47]. Older adults may also have added health benefits from this type of interaction [48]. Dietetic students benefited from the practical training experience, while older adults benefited from the socialization.

### Measurements

Table 2 lists all the measurements incorporated in the study.

**Table 2. T2:** Overview of measurements applied in the digital nutrition intervention study.

Measurement		Data collection timeline	Outcomes
Diet Quality Score		Measured at all data collection timepoints.	Developed to assess diet quality and nutrition risk [38]. Completed within 15 minutes and used to assess the Diet Quality Score [49]. Score based on overall diet quality (greater than 75=not at risk, between 60‐75=possible risk, less than 60=at risk) [50].
Healthy Eating Index (ASA24 Food Recall)		Prior, during, and after the assigned cohort intervention.	Measurement of dietary quality on recommendations from the Dietary Guidelines for Americans [51]. Completed using the Automated Self-administered 24-Hour Dietary Assessment (ASA24) online tool developed by the National Cancer Institute [52]. Research team will assist participants in the completion of the ASA24 food recall. Scoring is on a scale of 1 to 100 for the following food groups: fruits, vegetables, greens, whole grains, dairy, protein, seafood, plant proteins, fatty acids, refined grains, sodium, added sugars, and saturated fats [51].
Food security		Measured at all data collection timepoints.	Helps to determine financial barriers for safe access to food in the last 3 months [53]. The 10-question US Adults Food Security Survey Module will be used to assess food security in the following categories and score: 0=high food security, 1‐2=marginal food security, 3‐5=low food security, ≥6=very low food security [54].
Physical Activity Scale for the Elderly (PASE**)**		Measured at all data collection timepoints.	Used to assess self-reported physical activity in community-dwelling older adults over 7 days by adults aged 65 years and above [55]. PASE scores range from 0‐400 or more and are closely associated with grip strength and balance [55].
Short Physical Performance Battery (SPPB)		Prior, during, and after the assigned cohort intervention.	Developed by the National Institute of Aging to assess lower extremity functioning in older adults. SPPB includes gait speed, chair stand, and balance tests [56]. Overall scores can range from 0 (worst performance) to 12 (best performance) and are predictive of risk for frailty, mortality, nursing home admission, and disability [57].
Attitudes Toward Computers Questionnaire (ATCQ)		Measured at all data collection timepoints.	9-question Technology Attitudes Survey is used to measure a person’s comfort and interest in tablet computers [43,58,59]. Participants complete a 20-question survey rated on a 5-point Likert scale (strongly agree to strongly disagree). The final score is computed by adding scores from all questions.
Technology use questionnaire from the National Health and Aging Trends Study (NHATS)		Measured at all data collection timepoints.	9-question Technology Access and Usage Survey is used to measure technology comfort, typical daily use, and access in older adults [60]. Overall scores range from 0 to 9. A score of 0‐1 is classified as poor technology access and usage, scores of 2‐5 indicate moderate access and usage, and a score of 6‐9 signifies good technology access and usage.
OATS^a^ technology survey		Administered before, during, and after the 5-week technology essentials class.	Internal satisfaction survey following the completion of the 5-week technology essentials course administered by OATS. The data obtained from this survey will be used to evaluate the participants’ technology proficiency before and after the course, as well as to measure their satisfaction with the course materials, content, level of difficulty, and the instructor.
Social Disconnectedness Scale and Perceived Isolation Scale		Measured at all data collection timepoints.	Scale measures the degree of social isolation using two scales. The Social Disconnectedness Scale includes 13 items including restricted social networks and social inactivity [61]. The Perceived Isolation Scale includes 10 items including lack of support and loneliness [61].
3-item UCLA^b^ Loneliness Scale		Measured at all data collection timepoints.	The questionnaire assesses the degree of perceived loneliness using the 3-item UCLA Loneliness Survey (PhenX Toolkit) [62].
Malnutrition – Mini Nutrition Assessment (MNA)		Measured at baseline, 6 months, and 6-month postintervention.	5-question Mini Nutrition Assessment Short Form (MNA-SF) will be used as a screening tool to identify older adults who are malnourished or at risk for malnutrition [63]. Score greater than or equal to 12 indicates normal nutritional status, a score between 11 and 8 suggests being at risk of malnutrition, and a score less than or equal to 7 indicates malnourishment [64].
Frequency of Forgetting questionnaire		Measured at baseline, 6 months, and 6-month postintervention.	Assesses subjective memory impairments in older adult participants [65]. Scoring is based on the following categories: major problems, some minor problems, and no problems.
Activities of daily living questionnaire		Measured at baseline, 6 months, and 6-month postintervention.	The PhenX Toolkit was used to assess activities of daily living at baseline, 6 months, and 12 months [66]. Participants completed a 16-question survey and ability to complete activities: bathing, grooming, dressing upper body, dressing lower body, feeding, using toilet, walking, and getting in/out of chair.
Height, weight, and BMI		Measured at baseline, 6 months, and 6-month postintervention.	Measured without shoes and with lightweight clothing using a calibrated scale (Seca 876) and portable stadiometer (Seca 213). BMI will be calculated from the measured height and weight and will be used as part of the MNA score calculation. BMI categories are classified as follows: BMI less than 19=0, BMI 19‐20.9=1, BMI 21‐22.9=2, and BMI 23 or above =3 [67].
Demographic information and medical history		Gathered during screening.	Gathered responses on age, sex, residence zip code, senior center attended, race/ethnicity, who lives in the household, how many people live in the household, annual household income, education (highest level attended), current employment status, history of smoking, whether receiving benefits such as social security, disability, Supplemental Food Assistance Program (SNAP) or retirement benefits, diagnosis of medical conditions, and medication list.

a OATS: Older Adults Technology Services.

b UCLA: University of California, Los Angeles

### Process Evaluation

The process evaluation design is informed by the National Institutes of Health Behavior Change Consortium Treatment Fidelity Workgroup’s best practice recommendations [68]. Multiple indicators will be used to evaluate the fidelity and completeness of the implementation of all intervention components and determine the contribution of each component to the primary and secondary outcomes. All process evaluation measures present a minimum participant burden. Three major aspects of process evaluation will be measured. First, the intervention dose delivered (ie, the extent to which the technology and nutrition intervention is delivered as planned to older adult participants) will be measured by: (1) technology use records that will measure the times the participant interacted with the intervention materials; (2) completion of delivery schedule from OATS staff to indicate technology equipment and support has been delivered to the participants; (3) evaluation of staff training; and (4) monthly auditing of intervention lesson delivery. Second, the intervention dose received (ie, the extent to which the older adult participants understand and learn the technology and nutrition knowledge and skills delivered in the intervention) will be assessed by: (1) attendance records collected when older adults log in to the intervention site; (2) pre and post knowledge test after each intervention activity; and (3) poststudy focus groups on program delivery process and feedback with intervention staff (n=10). Third, participants’ responses to the intervention (ie, the extent to which the older adult participants use and apply the knowledge and skills learned in the intervention in daily life) will be evaluated by: (1) monthly surveys to gather feedback from older adults on their use and satisfaction with the intervention materials; and (2) poststudy focus groups with a subgroup of participants to assess their satisfaction with intervention components/activities and ideas for improving the intervention in the future.

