**Objective:**

The study aims (1) to test the impact of a digital nutrition education intervention on the primary outcomes of food security and diet quality; (2) to determine the effect of the intervention on secondary outcomes of technology knowledge and usage, physical activity, and social isolation and loneliness; and (3) to examine the long-term impact and sustainability of technology use on food security, diet quality, physical activity, social isolation, and loneliness.

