**Methods:**

This proposed digital nutrition education intervention study targets technologically limited older adults enrolled in the congregate meal program (CMP) using a stepped-wedge clustered randomized controlled trial. Key community partners, City of San Antonio Department of Health Services Senior Services Division and OATS, contributed to the study’s planning phase, research design, and implementation. The 20-week intervention included 5 weeks of in-person technology training, including internet access and technical support for 1 year and devices, followed by 15 weeks of a culturally tailored online nutrition education intervention. The study randomized 398 older adults from 12 congregate meal sites. Data collection took place at baseline, 3 months, 6 months, 9 months, 12 months, and 18 months. If successful, the impact of this program could be applied throughout the national OATS network and to similar CMPs to bridge the digital divide beyond the COVID-19 pandemic.

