#### Randomization and Allocation

Twelve out of the 14 centers participated in the study and were stratified by congregate meal participant enrollment and attendance as large (>100 participants), medium (50‐100 participants), and small (<100 participants) and randomly assigned to one of 2 start times: immediately (Cohort 1) or 6 months later (Cohort 2). Site randomization by a statistician occurred after participant recruitment; however, the treatment condition was not revealed to the participants. Neither the study participants nor the study staff were blinded to the treatment conditions.

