## Results

The project was funded in October 2022. As indicated in the study progress (Figure 3), recruitment and screening started in June 2022. The research team recruited and screened 150 participants by the end of August 2022 at the 7 original target centers. Due to the low recruitment numbers, the number of centers and recruitment time were extended. Seven additional centers for recruitment were incorporated starting in September 2022. Power analysis was completed to ensure adequate recruitment numbers were met with the 14 centers. NIH was notified in writing of these changes. Fourteen centers were condensed to 12 centers (1 closed because of structural damage and 1 smaller center merged with a larger sister center).

A total of 578 older adults completed the screening, of whom 507 participants were eligible to participate in the study (88%). The 12 centers were randomly assigned into 2 study cohorts, which consisted of a total of 398 older adult participants. Cohort 1 consisted of 226 eligible participants, of whom 164 participants graduated from the program. Cohort 2 had 172 eligible participants, of whom 111 participants graduated from the program (Figure 4). Monthly bingo and informative presentations (nonnutrition and nonphysical activity–related) were conducted with Cohort 2 centers for engagement and retention. Focus groups were conducted for Cohort 1 postintervention in October 2023 and for Cohort 2 in June 2024 to assess the fidelity of the intervention. Data collection for Cohort 2 is currently ongoing. Preliminary data analysis is being conducted for all cohorts to evaluate the intervention’s outcomes.

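### The process evaluation promises to determine each component's contribution to the outcomes, but a trial that randomizes only the start time of one bundled package cannot identify component effects

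*Protocol article*

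**What the plan says.** The Process Evaluation section lists delivery records, technology-use records, attendance, knowledge tests, surveys and focus groups. It says that these indicators will evaluate fidelity and also "determine the contribution of each component to the primary and secondary outcomes".

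The rest of the protocol article fixes what those indicators can draw on:

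- **Package.** The Abstract (Methods) describes one sequence: "The 20-week intervention included 5 weeks of in-person technology training, including internet access and technical support for 1 year and devices, followed by 15 weeks". Those last weeks are the online nutrition course. Under Technology Intervention, "enrolled participants received a technology bundle", with no subset excepted.
- **Randomization.** Under Randomization and Allocation, the centers were "randomly assigned to one of 2 start times: immediately (Cohort 1) or 6 months later (Cohort 2"). Nothing else is randomized.
- **Visits.** The Abstract (Methods) states: "Data collection took place at baseline, 3 months, 6 months, 9 months, 12 months, and 18 months".
- **Models.** Under Statistical Models, each aim uses a single treatment status, control or experimental. No component or dose term appears.
- **Control.** Under Participant Retention and Remuneration, Cohort 2 acts as an active control while waiting, with monthly wellness talks unrelated to nutrition and bingo.

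**The concern.** To determine a component's contribution to an outcome is a causal claim. It needs a contrast in which that component differs and the others do not, and in which the difference is not chosen by the participant. The article describes no such contrast. What is left is variation in how much each person used, which depends on who that person is. The Introduction itself reports that dropouts in a cited digital trial were mostly older, with poorer cognition and physical function.

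The stake is interpretation. The Abstract and Conclusions look ahead to use in other meal programmes, and Strengths and Limitations calls for low-cost internet and affordable devices. Adopters will therefore ask which part works. An association between usage and outcome, presented as a component's contribution, would answer that question without support from the design.

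**Working it through.** The article states no figure for component contributions, so there is none to reproduce. The check asks whether any contrast separates the components.

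**1. Randomized contrasts.** There are two start times and one package. Participants randomized to a subset of components: 0 of 398.

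**2. Power.** The sample-size section covers one two-group contrast. With effective N = 374 and effect size d = 0.41, the normal approximation gives power = Φ(d × √(N/4) − 1.96) = Φ(0.41 × √93.5 − 1.96) = Φ(2.00) = 0.977, which matches the stated 97.7%. No component effect is powered.

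**3. Visits against the programme timeline.** One month is 365.25/12/7 = 4.348 weeks. The technology part ends at programme week 5 and the nutrition part at week 20. Assume that the visit clock starts with the programme and that there is no gap between the parts:

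| Visit (month) | Week | Cohort 1 programme week | Cohort 2 programme week (start at month 6) |
|---|---|---|---|
| 0 | 0 | 0 | not started |
| 3 | 13.0 | 13.0 | not started |
| 6 | 26.1 | 26.1 | 0 |
| 9 | 39.1 | 39.1 | 13.0 |
| 12 | 52.2 | 52.2 | 26.1 |
| 18 | 78.3 | 78.3 | 52.2 |

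In each cohort the first visit after the start is 13.0 − 5 = 8.0 weeks into the nutrition course. The next follows the whole package. None falls at week 5.

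**4. How far that depends on the assumption.** Let s be the weeks from the start of the visit clock to the first technology class, and g the gap between the parts. The month 3 visit lies between the parts only if s + 5 ≤ 13.0 ≤ s + 5 + g, that is, s ≤ 8.0 and s + g ≥ 8.0. The Design section has Cohort 1 finish before Cohort 2 starts at month 6. If both run on the visit clock, s + g is at most 26.1 − 20 = 6.1 weeks, below the 8.0 needed. The month 3 visit would then fall between about 2 and 8 weeks into the nutrition course. Actual dates could still differ.

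**5. If a visit did fall at the boundary.** It would compare technology so far with the active control. Tablet, internet, support and class would remain bundled. The later increment would mix nutrition teaching with longer device use, activity videos and socials. Each component would still not be identified.

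**6. Remaining variation.** Log-ins and attendance are chosen by participants, the Zoom socials are optional, and peer navigators were recruited at most sites but not by random assignment. These can be correlated with outcomes, but the correlation mixes any effect of the component with the characteristics of those who took it up.

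**The case against.** The strongest reply is that nothing confirmatory depends on the clause. It sits in a fidelity section, no aim or hypothesis concerns a component, and the models and power deal with the whole package. That stands, and it limits the size of the point.

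A second reply is that a condensed article may leave the link between process measures and outcomes to a fuller document. That is fair for the method of analysis. It does not rescue the claim, because no analysis plan can create a randomized contrast that the design lacks.

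A third is that component-specific data exist: the technology provider's survey around the 5-week class, the knowledge tests and the focus groups. These can support exploratory or qualitative assessment. As described in Table 2, however, the survey covers proficiency and satisfaction, has no control-period counterpart, and does not measure food security or diet quality.

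A fourth is that the visit timing is not certain. Figures 1 and 3 are not shown, and Table 2 does not define the visit during the intervention for the Healthy Eating Index and the physical performance battery. Enrollment ended in December 2022 and Cohort 1 finished in August 2023, about 8 months for a programme of 20/4.348 = 4.6 months. The week 13 placement is therefore an assumption. The conclusion does not depend on it, as step 5 of the working shows.

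**Conclusion.** The clause is wrong as written. The design identifies one effect, that of the combined technology-plus-nutrition package against the active control, and cannot determine the contribution of its components. This rests on the stated randomization, package and models. The absence of a boundary visit adds to it, but only under the nominal schedule. The point is minor.

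Two stronger readings are tempting and are not supported:

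- **That the primary result is compromised, or will be credited to nutrition education alone.** The objective is phrased as "to test the impact of a digital nutrition education intervention on the primary outcomes of food security and diet quality", which could suggest this. But the Abstract (Methods) and Intervention Design both include the technology training in the intervention, and no passage attributes a difference to nutrition teaching alone. The whole-package comparison is unaffected.
- **That the graduation figures measure the problem.** In Cohort 1, 226 − 164 = 62 of 226 (27.4%) did not graduate. The Results also say: "Cohort 2 had 172 eligible participants, of whom 111 participants graduated from the program", which leaves 172 − 111 = 61 of 172 (35.5%). Graduation is not defined in the text. Non-graduation may mix withdrawal with low participation and, in Cohort 2, losses during the wait. It does not show how much of any component was used.

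**What to change.** In Process Evaluation, replace the promise to determine contributions with a statement that process measures describe fidelity, delivery and uptake, and that any association of component uptake with outcomes is exploratory and not an estimate of that component's effect. In the conclusions, state that the randomized effect is that of the combined technology-plus-nutrition package against the active control.

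Do not try to recover a causal dose effect with a complier analysis that uses randomized cohort as the instrument and graduation as the exposure. Non-graduates may have had the tablet, internet, class and part of the course. Assignment could then affect outcomes without graduation, and the exclusion restriction would fail.

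The cost is a few sentences. No new data or change to the primary analysis is needed. What is given up is a component-level claim that the trial could not have supported.
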